	2 — The team has an electronic patient record system that allows it to view changes in the patient health outcomes (nutritional and respiratory outcomes) over the course of several years
	3 — The team uses the electronic patient record system during the multidisciplinary staff meetings
	4 — The team displays information from the electronic patient record during the multidisciplinary meeting (graphs of changes over time, reports from previous consultations with different professionals, etc.)
	5 — The team uses the electronic patient record system both to create alerts on applying recommendations for the patient and to compile statistics on the population followed up
	6 — The team uses the electronic patient record system to include biology results
	7 — The team uses the electronic patient record system to include imaging results
	8 — The electronic patient record system helps in selecting patients for clinical trials
	9 — The electronic patient record data are automatically transmitted with a good degree of reliability (minimal verifications, corrections, and additions) to the French Cystic Fibrosis Registry
SN — Staff in the networks in the community	1 — The CFC has organized a network of professionals in the patient community for managing care at home
	2 — The CFC organizes regular trainings for professionals in the patient community
	3 — The CFC regularly evaluates the professionals caring for CF patients in the community
	4 — The CFC assesses the health providers of devices managing CF patients
	5 — The CFC assesses the needs for home care and its distribution between professionals and carers for a balanced organization of home care
	6 — The CFC provides the patients with offers of sports activities, creative activities, and psychological support near their place of residence

QT effectiveness has been described in the studies by Lemieux-Charles [17] and Shortell [18]: it is characterized according to 27 items (see Table 5).

**Table 5 Tab5:** Effectiveness of a quality team (QT)

Command of the quality process and tools	1. The teams that implement a quality process have a clear vision of the area on which to focus their improvement efforts and the expectations to be met. When you started the project, did you have such a vision?
	2. The quality teams sometimes use a method for making progress, such as a guide to follow step by step which helps them organize their work. Did your team use such a structured method?

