Effectiveness perceived by the rest of the team	1. I believe that the work of the steering team was useful for improving quality at the CFC.
	2. I believe that the entire team at the CFC was enlisted and contributed to quality improvement.
	3. I believe that the outcomes achieved collectively meet the organization’s needs for improvement.
	4. I believe that it is necessary to maintain an ongoing quality improvement process to continuously improve management at the CFC.

QT Internal factors that may have modulated the QT effectiveness: QT functioning [17] is characterized by 22 items classified in 4 categories 1) the organization at work, 2) the decision-making process, 3) the shared improvement goals, and 4) the ability to communicate and get external support. Studies by L. Lemieux-Charles defined these items to analyze the impact of adopting quality improvement practices on the internal functioning of a team. We use the same items to analyze if the team’s functioning could modulate its effectiveness (see Table 6).

**Table 6 Tab6:** Internal functioning of the quality team (QT)

Strictness of organization and clarity of roles	1. The leader was clear and explicit on how he or she wanted the team to work.
	2. The leader reviewed the steering team’s work and asked how we were going to go about it.
	3. The leader also requested the opinion of the other members of the team.
	4. The leader’s behavior reflected the importance he or she placed on the quality team functioning well.
	5. Our team could have been better at seeking help and securing more skills to do the work.
	6. Sometimes it seemed that we were working or going about the matter in the wrong way.
	7. Roles were so unclear that the work of different individuals seemed to overlap.
	8. The members of the team had different outlooks and experiences and came from different disciplines.
Decision- making on the QT	1. Most of the members of the team had an opportunity to participate in decision-making.
	2. We appreciated our differences, which shaped our decisions.
	3. The contribution of each member of the team was heard and taken into consideration.
	4. We examined many different ideas before making a decision.
	5. Our team possessed sufficient resources and skills and applied them well enough to work properly.
	6. Our team worked well enough to accomplish its mission satisfactorily.
Clarity of objectives	1. The members of the team were in agreement on the objectives of the project.

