### Development of the instruments of the realistic study

The self-administered questionnaire was developed from the instruments (cited above) translated into French, and new items prepared as part of this research to characterize quality of CF care and the degree of engagement of the patients or parents. The whole questionnaire is proposed to the members of the quality teams. A limited part of the questionnaire is proposed to the members of the MDT not on the quality team. The questionnaire has been prepared from January to June 2014 with clinicians from the Nantes/Roscoff CF-CERD and experts from the Health Education and Practice Laboratory (LEPS) at the Sorbonne Paris Cité University - Paris 13 Bobigny. It has then been tested between July and September 2014 in three teams from the Nantes/Roscoff CF-CERD (pediatric, adult, and mixed) with 29 respondents from all disciplines and the patients/parents participating in the QT. As a result of these tests, the questionnaire has been slightly adapted, essentially by rewording parts of the French translation and adding free text fields (*Questionnaire available upon request to the corresponding author*).

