### Analyses of responses and validation of the questionnaire

Responses to the items of the questionnaire are processed anonymously. Each item receives a score on a Likert scale from one to four based on the degree to which the respondent agrees or disagrees with the proposition: “Completely disagree; Disagree; Agree; Completely agree”. “No” and “Unknown” responses are assigned a score of 0. The score is reset to 100 points and can thus be totaled by theme of the questionnaire and category of respondents. An initial descriptive analysis of the responses by CFC is returned to each quality team in the month following the on-site investigation, via a web conference, in order to validate the interpretation of the scores for the different themes and identify avenues for or obstacles to continuous care quality improvement at the CFC.

A Cronbach’s alpha test will be performed on all responses collected at the centers. Since the anticipated number of respondents is around 130 people in total for the 14 teams, this test will not allow the questionnaire to be modified for use in a larger population of respondents. It mainly aims to validate the French translations of the parts of the questionnaire coming from previous studies in English and discuss the use of the parts created within this research study.

A second level of descriptive analysis will be performed by aggregating the responses (all CFCs, by professional discipline, for resource patients/parents, and for professionals) to search for potential associations between quality of care at the CFC 3 years after the PHARE-M intervention and the effectiveness of the QT and/or the engagement of parents/patients and/or contextual elements.

After the publication of the Registry report presenting the 2015 data, changes in indicators from 2011 to 2015 will be crossed with the results of the realistic part of the study, in an attempt to identify any association in relation with more favorable changes over time in patient outcomes. A “signature” set of factors associated with a maximum/minimum impact of the PHARE-M will be sought.

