### Limitations identified and initial lessons

As a result of the experimental study based on Registry data, a study population paired between two groups (intervention and control) was defined to eliminate certain confounding factors, especially factors linked to patient age distribution. Despite this pairing, significant differences remained in terms of patient age at diagnosis and primary endpoint (FEV1%) between the two groups before the intervention, in favor of the intervention group. These initial differences could have a favorable effect for the rate of decline in FEV1% in 4 years in the intervention group [22, 23]. The question is to investigate whether the slopes are parallel or not. The difference in FEV1% will be taken into account using two different intercepts in the model, one for the intervention group and one for the control group. The patients belonging to either the “PHARE-M” group or the “Control” group will be identified in the Patient Registry with respect to their group for further analysis of their health outcomes.

Moreover, on-site quality audits of the Registry data included in the calculation of the primary endpoints showed discrepancies, mainly due to the CFCs’ interpretation of the rule for selecting the values to transmit to the Registry [16]. The volume of the discrepancies identified in the data audited could be attributed to the change of the rule applied from the 2011 registry survey. This audit points out the need for a certification process to enable a larger use of this database in epidemiologic studies or for public health or pharmacovigilance purposes.

The survey conducted for the qualitative study of the multidisciplinary teams at the 14 centers should include around 130 respondents, including at most 14 patients/parents. This number of respondents might seem low for having enough statistical power in the statistical validation of the survey instruments, especially for the parts of the questionnaire developed within this research. The survey instruments could be improved within the framework of subsequent research studies aiming, for example, at comparing quality of care between centers trained in the PHARE-M and centers untrained in the program, or at making an assessment of the quality of care before/after another intervention. Therefore, this questionnaire represents an instrument that could have further uses in the network.

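### Cronbach's alpha is given the aim of validating the French translations, but it measures only the internal consistency of the French answers and cannot show equivalence with the English originals

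*Protocol article*

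**What the plan says.** The section on analysis of responses and validation of the questionnaire names one statistic for the purpose: Cronbach's "alpha test will be performed on all responses collected at the centers". Its aim is stated directly: "It mainly aims to validate the French translations of the parts of the questionnaire coming from previous studies in English". A second aim is to discuss the use of the parts written for this project. No acceptance threshold is given, and the section does not say whether alpha is computed per theme or over each instrument. It does say that scores are totaled by theme and by category of respondent.

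On size, "the anticipated number of respondents is around 130 people in total for the 14 teams", and not all of them answer everything: "A limited part of the questionnaire is proposed to the members of the MDT not on the quality team" (Development of the instruments of the realistic study). That section also reports a pre-test with 29 respondents in three teams, after which parts of the French were reworded.

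Among the parts taken from earlier studies, quality-team functioning "is characterized by 22 items classified in 4 categories" (Table 6), and quality-team effectiveness is said to have 27 items (Table 5). The 47-item care-quality list (Table 4) was adapted within the project.

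The limitations section says the number of respondents may be low for validating the instruments, and adds that "this questionnaire represents an instrument that could have further uses in the network".

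**The concern.** The article assigns a named test a property that the test does not have. Alpha is a function of the variances and covariances of the French responses. No English-version data enter it. If the French wording shifted the meaning of a whole set of items in the same direction, those items could correlate as well as before, and alpha would not register the change.

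The caveats given concern the number of respondents. That is a different limit: more respondents would estimate alpha more precisely, but would not turn it into a test of translation.

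What is at stake is what may be said about the instrument. The article looks ahead to later use of the questionnaire in the French network. A reported alpha could then be cited as evidence that the translations are valid.

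**Working it through.** The article states no alpha, threshold or target for the validation, so there is no figure to reproduce. The check asks how alpha responds when some items carry no information about the intended concept.

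**Inputs from the article**
- Table 6: 22 items in themes of 8, 6, 4 and 4.
- Table 5: 27 items stated. The table as it can be read lists 10 + 7 + 7 + 4 = 28, so both counts are used.
- Table 4: 47 items in themes of 4, 8, 14, 6, 9 and 6.
- About 130 respondents.

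**Assumptions (not in the article)**
- Mean inter-item correlation r among sound items: 0.30, with 0.20 and 0.40 as the range.
- A failed item is uncorrelated with all others.
- 0.70 is used only as a reference value for alpha.

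**Step 1. Item count.** Standardized alpha = k·r / (1 + (k − 1)·r).
- With r = 0, alpha is 0 for every k. Length alone produces nothing.
- Length amplifies a weak correlation. The r that gives alpha = 0.70 is 0.70 / (k − 0.70(k − 1)). For k = 22 this is 0.70/7.3 = 0.096; for k = 27 it is 0.70/8.8 = 0.080; for k = 8 it is 0.70/3.1 = 0.226; for k = 4 it is 0.70/1.9 = 0.368.

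**Step 2. Failed items.** With m of k items failed, alpha = k/(k − 1) × S/(k + S), where S = (k − m)(k − m − 1)·r.
- Example: k = 22, m = 6, r = 0.30. S = 16 × 15 × 0.30 = 72, and alpha = 22/21 × 72/94 = 0.80.
- Example: k = 8, m = 2, r = 0.30. S = 6 × 5 × 0.30 = 9, and alpha = 8/7 × 9/17 = 0.61.

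| Scale | Failed items | r = 0.20 | r = 0.30 | r = 0.40 |
|---|---|---|---|---|
| 22 items (all of Table 6) | 0 | 0.85 | 0.90 | 0.94 |
| | 6 | 0.72 | 0.80 | 0.85 |
| | 11 | 0.52 | 0.63 | 0.70 |
| 27 items (Table 5, stated) | 0 | 0.87 | 0.92 | 0.95 |
| | 7 | 0.77 | 0.84 | 0.88 |
| | 14 | 0.56 | 0.66 | 0.72 |
| 28 items (Table 5, listed) | 0 | 0.88 | 0.92 | 0.95 |
| | 7 | 0.78 | 0.85 | 0.89 |
| 8-item theme | 0 | 0.67 | 0.77 | 0.84 |
| | 2 | 0.49 | 0.61 | 0.69 |
| | 4 | 0.26 | 0.35 | 0.43 |
| 4-item theme | 0 | 0.50 | 0.63 | 0.73 |
| | 1 | 0.31 | 0.41 | 0.50 |
| | 2 | 0.12 | 0.17 | 0.22 |

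Over a whole instrument, about a quarter of the items can fail with alpha still at a level usually read as acceptable. On short themes, the same share of failures lowers it clearly.

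**Step 3. Shifted meaning.** If all items keep their mutual correlations but mean something other than the English items, m = 0 and every alpha equals its first-row value. Neither scale length nor sample size changes this.

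**Step 4. Sample size.** The Feldt 95% limits are 1 − (1 − alpha)·F, with F the 0.975 and 0.025 quantiles on n − 1 and (n − 1)(k − 1) degrees of freedom. For an observed alpha of 0.70, n = 130 and k = 22, they are 0.62 and 0.77. This imprecision is the kind of limit the article acknowledges, and it is separate from Step 3.

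**The case against.** A reader might infer that alpha will come out high from item count alone, so that validation would appear achieved however poor the translation. The documents do not support that.
- At zero inter-item correlation alpha is 0 whatever the length, and garbled items lower it clearly on 4- to 8-item themes.
- Scores are totaled by theme. If alpha follows the themes, a weak mean correlation of 0.15 gives only 0.41 (4 items) to 0.71 (14 items) across Tables 4 to 6. That would tend to look poor rather than good.
- No threshold is set, so nothing is formally passed.
- The 47-item list, where length would inflate alpha most, was adapted in the project. For the parts created in the project, the article promises only to discuss their use.

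The article is also more careful than a bare reading suggests. It says the test will not allow the questionnaire to be modified for a larger population, and that the instruments could be improved in later research. It reports a pre-test with rewording and returns scores to each team to check their interpretation. A condensed article may also leave translation procedures to a fuller protocol, so the absence of a described back-translation is not held against it.

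All of this stands and limits the point. It does not remove it. The pre-test and the team feedback address wording and interpretation within the French version, not equivalence with the English. The stated aim of alpha is in the text itself, and alpha cannot deliver it.

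**Conclusion.** The point holds as a mismatch between a named statistic and its stated aim. Alpha can describe the internal consistency of the French scales; it cannot validate the translations. That conclusion needs no numerical assumption.

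The numerical part is conditional. Only if alpha is run over the whole 22-item or 27/28-item instruments, which the text leaves open, can it stay at 0.80 to 0.85 with about a quarter of the items uninformative at r = 0.30 (0.72 to 0.89 for r from 0.20 to 0.40). On short themes alpha does respond to failed items.

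The importance is minor. This is a secondary, descriptive component, and the FEV1 and BMI comparisons are not touched. What changes is the claim that can be made for the questionnaire in later use.

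**What to change.** - Restate the aim of alpha as describing the internal consistency of the French scales.
- Report alpha per theme, with the mean inter-item correlation or the item-total correlations, so that single failing items can be seen.
- Remove the statement that alpha validates the translations. Say instead that the French wording was pre-tested in 29 respondents and that alpha does not establish equivalence with the English versions.
- For the 47-item care-quality list, do not treat a high or low alpha as evidence for or against validity. Its items cover separate features of a center, such as staffing, round-the-clock cover, electronic records and community networks, and need not correlate.

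The cost is a few sentences and a small addition to the planned output, with no new data. The downside is a weaker claim for the questionnaire.

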**Fig. 3 Fig3:**
[figure not shown]
Modeling of the intervention, context, and mechanisms

The PHARE-M intervention consisted of establishing, training and coaching a quality team (QT) at each CFC comprising a number of professionals from the multidisciplinary CF team and 1 parent or patient from the CFC’s caseload. The members of the QT have been trained in quality methods and tools and coached in changing care processes. The PHARE-M intervention should have directly impacted the ability of the local QT to master QI methods and tools, lead changes in the care processes, and should have generated good appreciation of the utility of the QT efforts. This direct impact of PHARE-M is identified under the heading “QT effectiveness”. QT effectiveness may not only be the result of the PHARE-M intervention but may have been modulated by internal mechanisms, such as the composition of the QT (number of members and disciplines enlisted), its functioning (rigor in the QI work, decision-making, clarity of the roles…) and the parent or patient engagement. Those mechanisms are represented as impacting QT effectiveness (Table 3). Beyond the ability to master the QI methods and tools, the PHARE-M intervention was expected to have an impact on the quality of CF care delivered at the CFC. The Chronic Care Model [12] was deemed appropriate to account for quality of CF care across the 6 dimensions: existing improvement goals, multidisciplinary care, self-management support, decision support (use of evidence-based guidelines), use of information system and electronic patient record, and organization of resources in the patient’s community of life. Finally, an indirect impact of the PHARE-M intervention is expected on the trend in patient outcomes’ evolution as measured in the quantitative part of this study. Moreover, some elements in the CFC contexts, which are external to the PHARE-M intervention and preexisted to its introduction, may have had a major impact both on the adherence of the team to the QI work and on its outputs. The contextual elements that have been brought in this study include the composition of the MDT, the leadership, the patient-centeredness of care, the innovative culture of the team, and the support from the hospital quality department.

The qualitative study will test these hypotheses using a questionnaire to be self-administered, in 2015, to all members of the MDT at the 14 CFCs and to the patients/parents participating in the quality teams.

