Quality of care has been defined according to the criteria of the Chronic Care Model [12]; as this model has not been popularized in France nor in cystic fibrosis, we adapted it with 47 items aimed at characterizing CF care. Table 4 presents a list of these items.

**Table 4 Tab4:** Criteria for quality of CF care derived from the chronic care model

IG — Improvement Goals at the CFC	1 — There are improvement goals at the CFC
	2 — These goals, if they exist, are the subject of both indicators and an action plan at the CFC
	3 — The CFC has tools to follow up this action plan in the form of a dashboard
	4 — To your knowledge, this action plan has been discussed with management and validated
SMS — Self-Management Support - Therapeutic Patient Education	1 — To your knowledge, there is a therapeutic education program for patients at the CFC authorized by the French regional health agency (ARS)
	2 — In your opinion, the professionals at the CFC are well trained in TPE
	3 — More than 80% of the patients/parents attended at least one TPE session in the last year
	4 — The total time spent by the professionals on TPE is sufficient
	5 — There are no obstacles to implementing TPE at the CFC
	6 — The team is involved in the studies of one of the French national groups on therapeutic education via face-to-face participation or regular reporting of information
	7 — The CFC has priority objectives for developing TPE
	8 — If yes, the CFC has indicators to follow up the achievement of these priority objectives
MM — Multidisciplinary management	1 — To your knowledge, the multidisciplinary team at the CFC comprises all the disciplines recommended by the French National Diagnosis and Treatment Protocol (PNDS): specialist physician, nurse, physiotherapist, psychologist, secretary, and social worker
	2 — The number of staff in all disciplines is sufficient for the number of patients followed up
	3 — In your view, the multidisciplinary team seems stable over time (the professionals’ turnover rate is below 20% in a year)
	4 — The members of the multidisciplinary team have a great deal of expertise in managing cystic fibrosis
	5 — The multidisciplinary team meets often enough to perform a summary of the records of the patients who have come to the CFC
	6 — During these multidisciplinary meetings, the team generally reviews the records of the patients with a scheduled visit to the CFC

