	3. Did your team make one or more changes in its way of working?
	4. Did the team analyze data to ensure that such change(s) indeed represented an improvement?
	5. Did the team try to understand variations in the CFC processes and the reasons that could account for them (variations over time or between professionals, time of year, patient characteristics, etc.)?
	6. Does the team routinely have data allowing it to make a state of play and identify problems?
	7. Did the team have to develop a system to collect specific data (such as questionnaires, audits, interviews, or measurements) to identify problems and assess the responses provided?
	8. Did the team establish a data collection system to continue to manage quality or monitor the new processes established?
	9. Was the team able to rely on a referent professional to coordinate the meetings and work of the quality team?
	10. Was the team able to rely on a referent professional to collect and analyze data?
	1. The team was able to perform measurements to define and assess changes within the framework of tests.
Capacity to drive change	2. After testing a change, the team succeeded in discussing the outcomes observed and learning from this test.
	3. The team succeeded in analyzing the outcomes of the test to propose new changes or adjustments to be tested.
	4. During the process, the team was able to easily incorporate and adapt ideas for changes to meet the organization’s needs.
	5. The team was able to enlist sufficient knowledge and skills to drive change under good conditions.
	6. The team could find sufficient assistance in the hospital to support changes.
	7. The team could sufficiently rely on the support of the French national team to make changes at the CFC.
Effectiveness perceived by the quality team	1. The performance of the PHARE-M steering team met my expectations.
	2. I was satisfied with my experience as a member of the quality team.
	3. I believe that my participation was useful and positive for the work of the team.
	4. I would be willing to participate again on a similar team to work on quality improvement.
	5. I believe that the work of the quality team was useful for improving quality.
	6. The outcomes achieved through the work of the quality team meet the organization’s needs for improvement.
	7. It is necessary to maintain an ongoing quality improvement process to continuously improve care at the CFC.

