The context elements include: the composition of the multidisciplinary team at the beginning of the PHARE-M intervention (2011) because it might have been a limiting factor in assigning staff to the QT; the culture of the microsystem to which the QT belongs [18] i.e. the organizational culture (see Table 8) and patient centeredness and leadership style (see Table 9); the alignment of the PHARE-M QIP with the hospital quality policy as described within the framework of the European QUASER study [20] using eight open questions in an interview with a head of the hospital quality department (see Table 10).

**Table 8 Tab8:** Organizational culture

*Organizational culture:*	
Research studies have defined four types of organizational culture, arising from both the organization’s external environment and internal management: a “familial” type, an “entrepreneurial” type, a “prescriptive” type, and a “productive” type. The five rubrics below describe the characteristics associated with these different types of organization. You have 100 points to distribute among the four proposals based on the degree to which they resemble your organization. For example: If the CFC resembles Description A a great deal and Description B a little, and does not resemble Description C or Description D at all, assign 70 points to Response A and the 30 remaining points to Response B.	
§1. Character	1. Organization A is very familial, like a big family. People seem to share a lot of themselves.
	2. Organization B is very dynamic and entrepreneurial. People seem to want to venture off the beaten path and take risks.
	3. Organization C is very structured and formalized. Procedures govern people’s work.
	4. Organization D is very focused on production, with the concern being that the work gets done. Individuals are not very personally involved.
§2. Management	5. Organization A’s director(s) are warm and attentive. They try to develop people’s potential and act as mentors or guides.
	6. Organization B’s director(s) take risks. They encourage people to be innovative and to try out new ideas by taking risks.
	7. Organization C’s director(s) enforce rules. They expect people to strictly apply policies and procedures.
	8. Organization D’s director(s) resemble coordinating coaches. They help people achieve the organization’s objectives.
§3. Cohesion	9. Organization A’s factors for cohesion are loyalty and tradition. Dedication to the organization is high.

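### The explanatory themes and the care-quality score come largely from the same respondents, and a few items sit on both sides, so associations between questionnaire scores are inflated

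*Protocol article*

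**What the plan says.** All references are to the Protocol article.

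- **Model.** Under 'Qualitative study', 'Design', QT functioning and patient/parent engagement are mechanisms that may modulate QT effectiveness. Care quality is a further result, in six dimensions. Five contextual elements are named: "the composition of the MDT, the leadership, the patient-centeredness of care, the innovative culture of the team, and the support from the hospital quality department". They are described as elements "which are external to the PHARE-M intervention and preexisted to its introduction".
- **Analysis.** 'Analyses of responses and validation of the questionnaire' states that "A second level of descriptive analysis will be performed by aggregating the responses". The aim is to "search for potential associations between quality of care at the CFC 3 years after the PHARE-M intervention and the effectiveness of the QT", and likewise with engagement and context. No test, significance level or unit of analysis is given.
- **Respondents.** 'Development of the instruments of the realistic study' gives QT members the whole questionnaire. Other members of the multidisciplinary team (MDT) receive a limited part, which is not specified. About 130 respondents are expected from 14 centers, each visited once for 2.5 days ('On-site investigations').
- **Other sources.** Hospital quality policy comes from an interview with a head of the hospital quality department (Table 10). MDT composition refers to 2011, with no source stated. Registry changes from 2011 to 2015 are later crossed with the survey results.
- **Limitations.** 'Limitations identified and initial lessons' mentions the low number of respondents. It mentions neither shared raters nor overlapping items.

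**The concern.** Two features push the correlations between questionnaire scores upward whatever the truth.

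1. **Same rater.** A generally favourable or critical QT member moves the explanatory score and the care-quality score in the same direction. Scoring both 'No' and 'Unknown' as 0 may add to this, because a poorly informed respondent lowers every theme in which those answers are used.
2. **Shared content.** The model treats functioning as a cause of effectiveness, yet part of the functioning scale asks how effective the team was.

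These associations are meant to show what makes PHARE-M work in some centers, and they inform the recommendations for national roll-out. If rating tendency is read as a working mechanism, the advice to the remaining centers will name factors that the data do not support.

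**Working it through.** **Step 1: item counts.** Table 4: 4 + 8 + 14 + 6 + 9 + 6 = 47, as stated. Table 6: 8 + 6 + 4 + 4 = 22, as stated. Table 5: 10 + 7 + 7 + 4 = 28 listed, against 27 stated. I use 28.

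**Step 2: content set side by side.**

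| Explanatory side | Result side | Match |
|---|---|---|
| Table 6 'Decision-making' item 5 (enough resources and skills, well applied) and item 6 ("Our team worked well enough to accomplish its mission satisfactorily") | Table 5 'Capacity to drive change' item 5 (enough knowledge and skills enlisted) and the perceived-effectiveness items | Close |
| MDT composition, 2011 | Table 4 MM1 (all disciplines present) and MM2 ("The number of staff in all disciplines is sufficient for the number of patients followed up"), rated in 2015 | Looser |
| Support from the hospital quality department (interview) | Table 5 'Capacity' item 6 ("The team could find sufficient assistance in the hospital to support changes") | Looser |

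Leadership, culture and patient orientation have their own tables (8 and 9) and are not items of Tables 4 or 5.

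**Step 3: weight of the looser overlaps.** Let k of N items be shared and uncorrelated with the rest, with inter-item correlation ρ within each block (assumed 0 to 0.5). The correlation of the score with its own shared items is

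r = √[Vs / (Vs + Vr)], where Vs = k + k(k−1)ρ, Vr = m + m(m−1)ρ and m = N − k.

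- MM1-2 in all 47 items: ρ = 0 gives √(2/47) = 0.21; ρ = 0.5 gives √(3/1038) = 0.05.
- MM1-2 in the 14-item MM theme: √(2/14) = 0.38 down to √(3/81) = 0.19.
- 'Capacity' item 6 in all 28 items: √(1/28) = 0.19 down to √(1/379) = 0.05.
- 'Capacity' item 6 in its 7-item theme: √(1/7) = 0.38 down to √(1/22) = 0.21.

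These figures are bounds for illustration. They would describe the planned analysis only if the predictor were the shared items themselves. It is not: one predictor is 2011 composition and the other comes from a separate interview.

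**Step 4: same-rater effect.** If a share c of the variance of each of two scores is one common respondent tendency, and nothing else links them, their correlation is c. With Fisher's z,

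P(nominal p < 0.05) = Φ(a − 1.96) + Φ(−a − 1.96), where a = atanh(c)·√(n − 3).

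| c (assumed) | n = 130 pooled | n = 14 centers |
|---|---|---|
| 0.1 | 20% | 6% |
| 0.2 | a = 0.2027 × 11.27 = 2.28: 63% | a = 0.2027 × 3.317 = 0.67: 10% |
| 0.3 | a = 0.3095 × 11.27 = 3.49: 94% | a = 0.3095 × 3.317 = 1.03: 18% |

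The right-hand column assumes that the same c holds for center means. Both columns are shown because the plan does not fix the unit. The groupings it lists (all centers, discipline, patients/parents, professionals) do not include the center. For the QT themes 130 is an upper limit, since other MDT members answer only part of the questionnaire.

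**The case against.** The strongest reply is that the analysis is descriptive, looks only for potential associations, and sits beside focus groups, hospital interviews and registry outcomes. No p-value is planned, so false-positive rates describe a test that nobody has promised. This stands as far as the percentages go: they illustrate the effect under assumed values and do not predict this study's results. It does not remove the bias, because a descriptive correlation is inflated in the same way. The planned Cronbach's alpha would not reveal it either: alpha measures consistency within a scale, and a common rating tendency raises it.

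Three stronger readings are tempting, and the protocol does not support them.

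- **That the associations arise by construction.** Only two of the five contextual elements touch Tables 4 or 5, through a few items. One of these is dated to 2011 and the other has a separate informant. The values 0.38 in step 3 are therefore not expected correlations.
- **That Table 4 IG 1-3 (goals, indicators, dashboard) contaminate the care-quality score.** Improvement goals are one of the six care-quality dimensions that PHARE-M is expected to change. A link with QT effectiveness there is part of the hypothesis.
- **That the signature of factors is compromised throughout.** It is announced directly after the crossing with registry outcomes, which do not come from these raters.

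It is also fair to say that the Table 6 items come from an existing instrument. That argues for keeping the full scale in the main analysis and using a reduced one only as a sensitivity score.

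**Conclusion.** The point holds as an upward bias in associations between questionnaire scores. It comes mainly from shared raters. Item overlap adds to it, most clearly between QT functioning and QT effectiveness. The direction assumes that all themes are scored so that higher is better. The size is unknown, because the protocol gives no inter-item or between-theme correlations. Under an assumed induced r of 0.2 to 0.3, the bias would dominate a pooled analysis of 130 responses and matter much less across 14 centers. That each respondent answers in a single sitting is implied rather than stated, and the conclusion does not depend on it. This is a worthwhile, inexpensive improvement to a secondary analysis. It does not invalidate the qualitative study.

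**What to change.** 1. **Separate the raters.** Beside the planned analysis, relate scores at center level with the explanatory score and the care-quality score taken from different respondents of the same center. If the limited questionnaire includes the care-quality section, use non-QT staff for care quality and QT members for the QT themes. Otherwise, split each center's respondents at random, repeat over many splits and average. With 130/14 = 9.3 respondents per center, a half is about 4 to 5 people, and fewer of them will have answered the QT themes. Responses are already analysed by center and respondent category, so nothing new has to be collected.
2. **Add an overlap-free sensitivity score.** Leave out Table 6 'Decision-making' items 5-6 when relating functioning to effectiveness, MM1-2 when relating care quality to MDT composition, and 'Capacity' item 6 when relating effectiveness to hospital support. Keep IG 1-3.
3. **State the limitation.** Say that an association seen only in the same-rater analysis may be due to the common source.

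The cost is some re-scoring and programming. The price is noisier scores, only 14 centers and smaller associations.
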